1. *Inter-rater reliability* will be assessed by having all research assistants observe and document the same three screening and baseline pilot interviews and having one member of the research team role play as a participant. Inter-rater reliability will then be quantified by the intraclass correlation coefficient (ICC 3,10) for all measures included in the assessments. This data has already been completed as part of the role-plays conducted during training, but the intraclass correlation coefficient has not yet been calculated.
2. *Test-retest reliability* will be assessed by having the first 24 pilot participants complete the screening and baseline assessments twice (one week apart, administered by the same research assistant) prior to commencing the pilot intervention. The correlation of a given measure between these two assessments will be calculated to determine test-retest reliability. This will be evaluated once all pilot assessments have been completed.
3. *Internal consistency* will be assessed by calculating Cronbach’s alpha for each measure as well as evaluating whether the reliability substantially improves upon removal of any single item. We will also calculate item-rest correlation to assess the correlation between a single item and the total scale score (excluding the item under study). Internal consistency will be evaluated once all pilot assessments have been completed.

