**V. Study Procedures**

In this section, provide details of your procedures, particularly as they relate to human subjects. If this is a multi-center study, make the role of JHSPH clear. If the JHSPH will serve as **data coordinating center**, indicate in the sections below which procedures JHSPH will not be performing. Additional information regarding data coordinating centers is requested in a later section. If your study will develop in phases, address each item below by phase.

A. Recruitment Process:

1. Describe how you will identify, approach, and inform potential participants about your study. Include details about who will perform these activities and what their qualifications are.

Ten research assistants have received 12 days of training on topics related to research methods, recruitment procedures, structured interviewing skills and other aspects of data collection. All research assistants have previous experience working in gender-based violence projects in the camp and/or data collection activities. Furthermore, all research assistants are Congolese refugees themselves. The leader of the research assistant team will request permission from the leaders of women’s groups in Nyarugusu to attend their next meeting. If permitted, two or more research assistants will attend the women’s group meeting and read a structured recruitment script that provides basic information about the study. The recruitment script does not explicitly state that the intervention is targeting women with a history of intimate partner violence and psychological distress in order to protect the privacy of individuals that express interest in participating. The research assistants request that interested individuals approach them after the women’s group meeting at which time they will provide more information about the program, including the sensitive aspects of it, and conduct the screening interview for eligibility.

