Prior to screening, one of the research assistants will obtain oral informed consent from the potential participant. During the research training all participants received 1.5 days of training in informed consent and related issues surrounding research ethics. All members of the research team are Congolese refugee women that have varying levels of experience working in gender-based violence programming and research. The consent discussion will occur in a private place either in the research team office or another private location requested by the participant. The oral consent describes the aims of the project, the purpose of screening, potential risks and benefits of screening, and protections for the patient (e.g. confidentiality, autonomy). The screening is estimated to take 20-30 minutes and is in the form of a structured interview. Based on the participant’s responses, the research assistant will be able to complete an eligibility assessment worksheet to determine whether the participant is eligible for enrollment into the trial. Adults lacking capacity to consent for the screening process will not be allowed to have a legally authorized representative provide consent at this phase. No children will be included in the study as per our eligibility criteria. There will be no witnesses included in the consent process.

*Consent for Enrollment (Written)*

Once participants are notified of their eligibility they will have the opportunity to continue with the baseline assessment or reschedule this for another time, if they are eligible for the trial. The baseline assessment is preceded by a written consent process that goes into much greater detail about the procedures for the trial (e.g. the intervention format), the time commitment and expectations, detailed risks and benefits of participation, as well as protections and contact information for investigators and IRB officials in case the participant has questions or concerns. This written consent phase will also be done 1-on-1 between a research assistant and a participant (there will be no witnesses). We will only consider consent to be obtained if the participant provides a signature indicating their voluntary participation or, in cases where the participant is not able to write, they will provide their thumbprint. No children will be included in the trial as per our eligibility criteria.

Figure 1. Enrollment Procedures

Recruitment

Oral consent for screening

Screening

Written consent for enrollment

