
Baseline assessment

*Process Evaluation (Oral Consent)*

All participants included in the process evaluation must provide oral consent to a member of the research team. The consent discussion will occur in a private place unless the participant requests otherwise and is comfortable discussing the themes of the process evaluation, which do not include personal or sensitive health information, in a public setting. The oral consent describes the purpose of the process evaluation, potential risks and benefits of participating, and protections for the patient (e.g. confidentiality, autonomy). The process evaluation is estimated to take 45-60 minutes and is in the form of an unstructured interview.

2. Identify the countries where the research will take place, and the languages that will be used for the consent process.

| Country | Consent Document(s)  (adult consent, parental permission, youth assent, etc.) | Languages |
| --- | --- | --- |
| Tanzania | Oral consent (screening) | Kiswahili |
| Tanzania | Written consent (enrollment) | Kiswahili |
| Tanzania | Oral consent (process evaluation) | Kiswahili |

*Note:* Congolese refugees in Tanzania speak Kiswahili, French and, in fewer cases, English. Kiswahili tends to be the language commonly spoken and it has developed into a hybrid form of Kiswahili incorporating elements of Tanzanian and Congolese Kiswahili. We have spent substantial time working with the research team and translators from Muhimbili University of Health and Allied Sciences (MUHAS) to adapt and translate our measures and consent form such that they reflect this type of Kiswahili (see certificate of translation).

C. Study Implementation:

Answer the following:

1. Describe the procedures that participants will undergo. If complex, insert a table below to help the reviewer navigate.

Recruitment and Screening: Contact with participants begins at recruitment. Participants will be recruited from women’s groups or on a referral basis at which time they will be invited to participate in a screening interview, which is preceded by an oral consent process.

Enrollment and Baseline Interview: If eligible, the research assistant then seeks written consent for enrollment followed by the baseline interview, which may directly follow screening or be rescheduled for another time in the upcoming week.

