| Identifying study assignment (based on participant’s women’s group affiliation indicated in baseline assessment) |  |  | X |
| Intervention sessions 1-8 |  |  | X |
| Post-intervention assessment |  | X |  |
| Participant retention (in intervention, intervention group only) |  |  | X |
| Participant retention (assessments, intervention and control group) |  | X |  |
| Process evaluation |  | X |  |
| Analysis and dissemination | X |  |  |
| Coordination of activities | X |  |  |

JHU: Johns Hopkins, MUHAS: Muhimbili University of Health and Allied Sciences, IRC: International Rescue Committee

1. Describe the number and type of study visits and/or contacts between the study team and the participant, how long they will last, and where/how they will take place.

Research Study Visits: All participants will complete 2-4 research study visits: screening/baseline which may take place in a single or two separate study visits, a post-intervention interview and possibly, if randomly selected, a qualitative process evaluation interview. The screening is estimated to take approximately 20-30 minutes. The baseline and post-intervention interview are estimated to take approximately 1.5 hours. The qualitative process evaluation is estimated to take between 45-60 minutes. All research visits will take place either at the research team office, which is located in the International Rescue Committee education center in the camp, or at a private location of the participant’s choice. Participants randomized to the intervention will also have 8 intervention visits. Intervention visits last anywhere from 1.5-2 hours each and will take place at existing International Rescue Committee private meeting spaces in the camp.

In addition to the regular study visits, a random 10% of participants will be contacted by the research team leader to confirm that the research assessments took place as intended for quality assurance and data collection monitoring purposes. The research team leader will contact selected participants preferably by phone, or in person if they are unreachable, and ask them the following questions:

1. Did a member of the study team complete the scheduled research assessment?
2. Approximately how long did the assessment last?
3. What was the name of the research assistant that conducted the interview?

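### Inter-rater reliability is specified as ICC(3,10), the consistency of a ten-rater mean, while each interview is described as done by one assistant, so the Aim 1 figure will overstate the reliability of the scores in use

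*Protocol*

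**What the plan says.** Section III, Aim 1, item 1 sets the design of the inter-rater exercise: "having all research assistants observe and document the same three screening and baseline pilot interviews and having one member of the research team role play". The statistic follows: "Inter-rater reliability will then be quantified by the intraclass correlation coefficient (ICC 3,10) for all measures included in the assessments". The same item says that these ratings were already collected during training and that the coefficient is still to be computed.

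The number of assistants is in section V.A: "Ten research assistants have received 12 days of training on topics related to research methods, recruitment procedures, structured interviewing skills".

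Four places bear on how many assistants take part in a real interview:

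- Pilot retest (section III, Aim 1, item 2): two assessments "one week apart, administered by the same research assistant".
- Screening (section V.B): "the research assistant will be able to complete an eligibility assessment worksheet to determine whether the participant is eligible for enrollment into the trial".
- Baseline (section V.C, procedures): "the research assistant then seeks written consent for enrollment followed by the baseline interview".
- Quality check on completed assessments (section V.C, study visits): "What was the name of the research assistant that conducted the interview".

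Section IV makes eligibility depend on an average score of at least 1.75 on either of two symptom checklists. The protocol gives no acceptance threshold for the ICC, no confidence interval and no single-rater coefficient.

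**The concern.** A reliability coefficient should describe the score that will be analysed. In the usual notation the first index of ICC(3,10) means a two-way model with fixed raters, measuring consistency. The second index means the mean of ten raters. Averaging over ten people cancels most of the individual recording error, so the coefficient can be high while any one assistant's score is only moderately reproducible. The study appears to use one assistant's score each time.

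The consistency form adds a second problem. If one assistant scores everyone somewhat higher than another does, that difference is removed before the coefficient is formed. For ranking women this may be harmless. For a fixed cut-off it is not, because a shift in level moves women across 1.75 in either direction.

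What is at stake is the Aim 1 conclusion. Section III gives the lack of validation of these tools in this population as the reason for the exercise, so its inter-rater result should not overstate how well one assistant's score can be reproduced.

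**Working it through.** **No figure to reproduce.** The protocol reports no ICC. The single-rater values below are assumptions, shown as a range.

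**Inputs from the protocol.** Raters k = 10 (section V.A). Rated interviews n = 3 (section III, Aim 1, item 1). Assistants per real interview: one, inferred from the four places listed above. No single sentence states it for every visit, but nothing contradicts it.

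**Step 1: from single-rater to ten-rater mean.** The two forms are linked by Spearman-Brown: ICC(3,k) = k·r / (1 + (k − 1)·r), where r is the single-rater consistency ICC. For r = 0.30: 10 × 0.30 / (1 + 9 × 0.30) = 3.0 / 3.7 = 0.81.

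| Assumed single-rater r | Reported ICC(3,10) |
| --- | --- |
| 0.05 | 0.35 |
| 0.10 | 0.53 |
| 0.20 | 0.71 |
| 0.30 | 0.81 |
| 0.50 | 0.91 |
| 0.80 | 0.98 |

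**Step 2: the reverse.** r = R / (k − (k − 1)·R), where R is the reported value. A reported 0.75 gives 0.75 / (10 − 6.75) = 0.23. A reported 0.90 gives 0.90 / (10 − 8.10) = 0.47. If the role-player is one of the ten assistants, k = 9 and the answers hardly change (0.25 and 0.50).

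**Step 3: precision with three interviews.** This takes the three interviews as the rated targets. For an observed single-rater consistency ICC of 0.30, F = 1 + 10 × 0.30 / 0.70 = 5.29 on 2 and 18 degrees of freedom. The 97.5% points are 4.56 for F(2,18) and 39.4 for F(18,2).

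- Lower: F_L = 5.29 / 4.56 = 1.16, and (F_L − 1) / (F_L + 9) = 0.02.
- Upper: F_U = 5.29 × 39.4 = 208, and (F_U − 1) / (F_U + 9) = 0.95.

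The 95% interval is about 0.02 to 0.95. It belongs to the consistency form, ICC(3,1); the absolute-agreement form needs its own interval.

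**Step 4: systematic differences between assistants.** Suppose, for illustration, that 30% of the variance is between interviews, 30% is level shifts between assistants and 40% is residual.

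- Single-rater absolute agreement: 0.30 / (0.30 + 0.30 + 0.40) = 0.30.
- Single-rater consistency: 0.30 / (0.30 + 0.40) = 0.43.
- Ten-rater-mean consistency: 0.30 / (0.30 + 0.40 / 10) = 0.88.

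The level shifts enter only the first of these.

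**The case against.** **Agreement may be high anyway.** The measures are self-report items given in structured interviews. Assistants watching the same role-play mostly write down the same spoken answers. If single-rater agreement is 0.80 or more, the reported 0.98 misleads little. This stands: nothing in the protocol shows that agreement is poor, and very poor agreement (0.05 or 0.10) would still show up as 0.35 or 0.53. The overstatement matters most between about 0.2 and 0.5.

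**The notation may be shorthand for three interviews by ten raters.** The numbers do coincide. The standard meaning is the likelier one after the letters ICC. On the other reading the form of coefficient is left open, and a single-rater coefficient is still not specified.

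**Fixed raters are reasonable.** All the assistants took part in the exercise, and the trial's own research staff carry out the pilot. This stands, but it defends the 3 and not the 10. A fixed-rater model can also be used with single-rater absolute agreement.

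**Stronger readings that the protocol does not support.** A reader might infer that a poor measure would be passed into the trial on this coefficient. No threshold or acceptance rule exists, and Aim 1 also draws on retest, internal-consistency, construct and content evidence. A reader might infer that the choice adds noise to the primary outcomes. Whatever noise exists is the same under any coefficient, and the ICC enters neither the sample-size formula nor the mixed models. A reader might infer that differences between assistants bias the comparison of arms. The protocol does not say how assistants are allocated to participants, which is not evidence of imbalance, and it keeps them blind to assignment.

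**Conclusion.** The point holds as a mismatch between the coefficient and its use. The protocol specifies the reliability of a ten-rater mean and uses scores that it describes as coming from one assistant. For assumed single-rater values of 0.20 to 0.50 the reported figure would be 0.71 to 0.91, and the gap shrinks as agreement rises. The conclusion rests on the standard reading of ICC(3,10) and on the inference of one assistant per interview. The choice of a consistency form is a second, smaller weakness, because eligibility is decided on a fixed score.

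The consequence is limited to the Aim 1 measurement validation. With three role-played interviews, no form of the coefficient is precise enough to accept or reject a measure.

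**What to change.** In section III, Aim 1, item 1, replace ICC(3,10) with a single-rater, absolute-agreement ICC and its 95% confidence interval as the inter-rater result. State whether raters are treated as random or fixed; either is acceptable. Keep ICC(3,10) at most as a supplement, labelled as the reliability of a ten-rater mean. Add a sentence saying that three role-played interviews serve as a training check and do not establish the inter-rater reliability of the tools.

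This needs no new data, because the ratings are in hand and the coefficient has not been computed. The only cost is a lower reported figure with a wide interval.

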**III. Study Design**

1. Provide an overview of your study design and methods. The study design must relate to your stated aims/objectives. Details will be requested later. If your study also involves analysis of existing data, please complete Section XI, “Secondary Data Analysis of Existing Data” in the last part of this research plan. If your study ONLY involves analysis of existing data, please use the research plan template for secondary data analysis (JHSPH IRB Research Plan for Secondary Data Analysis of Existing Data/Specimens).

AIM 1: Pilot measurement tools assessing identified priority mental health conditions, functional impairment and intimate partner violence in Nyarugusu refugee camp

We have selected measurement tools that have been used in previous research on mental health and IPV and were consistent with the priority mental health and psychosocial problems affecting female survivors of IPV in Nyarugusu identified in our previous qualitative research (please see section V.B.4 and attached measures). However, because these tools have not been validated in Congolese refugees residing in Nyarugusu refugee camp, we plan to conduct a validation study prior to starting the randomized controlled trial. For the validation study we will recruit 60 women from zone 1 meeting the eligibility criteria for the trial to complete the screening and baseline assessment and participate in the intervention during the pilot period. The measurement validation and pilot intervention activities will be implemented by the research staff and intervention facilitators hired to complete the randomized controlled trial. For purposes of measurement validation, we will not conduct the post-intervention assessment with the pilot participants because there are no new measures introduced during these assessments. Thus, completing the screening and baseline assessments during the pilot phase will be sufficient for completing our objective of evaluating the validity and reliability of these measurement tools among women in Nyarugusu. Using pilot measurement validation data we will be able to assess inter-rater reliability, internal consistency, construct validity, test-retest reliability and face/content validity as follows.

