**IV. Participants**

Describe the study participants and the population from which they will be drawn. Specify the inclusion and exclusion criteria. If you plan to include children, note their ages and whether you will include children in foster care. Note if the participants are particularly vulnerable in terms of cognitive limitations, education, legal migration status, incarceration, poverty, or some combination of factors.

Congolese refugee women residing in Nyarugusu camp in northwest Tanzania reporting a past-year history of intimate partner violence and experiencing moderate to severe psychological distress will be included in this study. We will initially invite women to participate that are members of women’s groups that operate throughout the camp. Women’s groups in Nyarugusu have been organized as a mechanism to strengthen social support among women in the camp. The types of women’s groups include cooking, weaving, tailoring and microfinance. Women’s groups are formed by IRC and other agencies in the camp; however, women from the community may propose to start a women’s group to these agencies as well. Each women’s group contains approximately 11-20 women and they each elect a leader that organizes group meetings and activities throughout the camp. Members organize most women’s group activities, however IRC and other agencies do occasionally provide skills trainings to women’s groups at the women empowerment center or other venues throughout the camp. In addition to recruitment through women’s groups, we will also include women that are referred to the program so long as they meet the following eligibility criteria:

1. Inclusion criteria:
   1. 18+ years of age
   2. Female
   3. Refugee from the DRC residing in Nyarugusu refugee camp
   4. Past-year history of intimate partner violence (survivor)
   5. Experiencing moderate to severe levels of psychological distress during the past month as measured by the 25-item Hopkins Symptom Checklist and the Harvard Trauma Questionnaire (Average Score >=1.75 on either checklist, indicating close to a moderate amount of distress)
2. Exclusion criteria:

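### Aim 1 judges test-retest reliability by a correlation alone, which cannot show a shift in scores between the two interviews; add the mean retest difference and an absolute-agreement ICC

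*Protocol*

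**What the plan says.** Protocol Section III (Study Design, Aim 1) has "the first 24 pilot participants complete the screening and baseline assessments twice", a week apart, with the same research assistant and before the pilot intervention begins. It then names the statistic: "The correlation of a given measure between these two assessments will be calculated to determine test-retest reliability". The type of correlation is not given. Neither a mean difference nor an agreement measure is mentioned.

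The item just before it does name an intraclass coefficient, but for a different purpose: "Inter-rater reliability will then be quantified by the intraclass correlation coefficient (ICC 3,10) for all measures". By its standard definition that is a consistency coefficient, which also removes mean differences.

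The women are a selected group: "we will recruit 60 women from zone 1 meeting the eligibility criteria for the trial". Section IV (Participants, inclusion criteria) sets the distress criterion at "Average Score >=1.75 on either checklist", referring to the past month, "as measured by the 25-item Hopkins Symptom Checklist and the Harvard Trauma Questionnaire".

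The construct-validity item in Section III carries the reliability coefficients into a multi-trait, multi-method matrix of correlations. No target reliability or expected change at retest is stated.

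**The concern.** A correlation measures whether women keep their relative positions. It says nothing about whether the whole group moved. Two features of this pilot make a movement plausible.

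- **Effect of the interview.** Section VII says that most participants find it cathartic to discuss these matters with research assistants, and Section VIII says that the assessments may be therapeutic in themselves. The recall period is the past month and the retest comes after one week, so roughly three of the four weeks overlap. A marked fall would therefore suggest a change in reporting or an effect of being interviewed.
- **Selection at screening.** Women enter because a checklist score was high on the first occasion, and the same checklists are then repeated.

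The retest is also the only planned look at repeated scores without treatment before the trial. Section III gives pilot women no post-intervention assessment and the pilot no control group. At stake are the Aim 1 statement that the scales are reliable here, and how a fall within one arm should later be read.

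**Working it through.** The protocol gives no reliability figure, so there is none to reproduce. Three things can be checked.

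**1. What a correlation misses.** If every score moves by d standard deviations and the SDs are equal, the correlation r is unchanged, and the single-measure absolute-agreement coefficient is

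ICC(A) = r / (1 + d²/2).

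With r = 0.80 (assumed):

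| Uniform shift d (SD) | Correlation | ICC(A) |
|---|---|---|
| 0 | 0.80 | 0.80 |
| 0.2 | 0.80 | 0.80/1.02 = 0.78 |
| 0.5 | 0.80 | 0.80/1.125 = 0.71 |
| 0.8 | 0.80 | 0.80/1.32 = 0.61 |
| 1.0 | 0.80 | 0.80/1.50 = 0.53 |

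**2. What selection does.** Take a normal true-score model with reliability R, selection at the median of one scale, R = 0.7, and scores in unselected SD units.

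- Mean of the first score among those selected: 0.798. Its variance: 1 − 2/π = 0.363.
- Expected fall with no true change: (1 − 0.7) × 0.798 = 0.24.
- Covariance of the two scores: 0.7 × 0.363 = 0.254.
- Variance of the second score: 0.49 × 0.363 + 0.51 = 0.688.
- Correlation: 0.254 / √(0.363 × 0.688) = 0.51.
- True reliability among those selected: (0.49 × 0.363 + 0.21) / (0.49 × 0.363 + 0.21 + 0.30) = 0.388/0.688 = 0.56.

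The correlation (0.51) therefore lies below the reliability in the selected women (0.56) and in the unselected population (0.70).

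The same model was simulated with the protocol's cut-off of 1.75. The protocol supplies the cut-off, the either-checklist rule and a baseline variance of 0.25 (SD 0.5; Section III, sample size). Assumed are an unselected mean of 1.5 to 2.0, SD 0.5 or 0.6, reliability 0.5 to 0.9, a true-score correlation of 0.7 between the checklists, and the screening score as the first occasion. For mean 1.75, SD 0.5 and the either-checklist rule:

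| Unselected reliability | True reliability, enrolled | Correlation | ICC(A) | Fall (points) |
|---|---|---|---|---|
| 0.50 | 0.44 | 0.40 | 0.39 | 0.071 |
| 0.70 | 0.62 | 0.59 | 0.59 | 0.045 |
| 0.80 | 0.72 | 0.71 | 0.71 | 0.031 |
| 0.90 | 0.85 | 0.84 | 0.84 | 0.015 |

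Across all 48 scenarios (either rule, and selection on one checklist alone) the correlation was below both reliabilities. Under the either rule the fall was 0.01 to 0.13 points, and the correlation exceeded ICC(A) by only 0.000 to 0.013. With selection on one checklist alone the fall was 0.03 to 0.33 points and the gap 0.005 to 0.096.

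**3. What 24 women can show.** Fisher's interval for an observed r = 0.80 is tanh(1.099 ± 1.96/√21) = 0.59 to 0.91. For the mean difference at r = 0.80, the SD of a difference is √(2 × 0.20) = 0.632 SD, so the 95% half-width is 2.069 × 0.632/√24 = 0.27 SD, or 0.13 points at SD 0.5. A shift of 0.5 SD would be visible in the mean difference.

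**The case against.** The case for leaving the plan alone has several parts, and some of it stands.

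- **The matrix needs correlations.** This stands. It is a reason to keep the correlation, not a reason to report nothing else.
- **The type is unnamed and could be settled in an analysis plan.** This stands in part: an absolute-agreement ICC is not excluded. But the protocol does name the statistic, uses the term ICC in the preceding item where it means one, and mentions no mean difference.
- **Under selection, an agreement ICC is further from the true reliability than the correlation is.** This is correct. With selection on one checklist at reliability 0.80 (mean 1.75, SD 0.5), the figures are 0.663 (true), 0.628 (correlation) and 0.593 (ICC). The ICC should therefore be added rather than substituted, and read with the selection in mind.
- **No shift is quantified.** This also stands. The protocol offers a reason to expect one, but no size.

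A reader might infer three stronger things, none of which the protocol supports. The first is that selecting high scorers makes the planned correlation overstate reliability; step 2 shows the opposite. Regression to the mean comes from the same random error that the correlation already reflects. The second is that the fall from selection rivals a treatment effect. It is 0.01 to 0.13 points under the protocol's rule, against a planned difference of 1.3 − 0.7 = 0.6. The third is that the trial result would be biased. Controls have the same screening, baseline and week-10 interviews, so a shift common to both arms cancels in the comparison.

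**Conclusion.** The point holds in a limited form. A correlation alone cannot reveal a systematic change between the two interviews, although the protocol itself suggests that interviewing may relieve distress. A real shift of 0.5 SD would leave a correlation of 0.80 untouched while absolute agreement fell to 0.71. That size is illustrative.

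For the two checklists used in screening, the correlation is also range-restricted. Under the either-checklist rule it came out 0.04 to 0.14 below the unselected reliability in the simulations, and some fall at retest is expected without any true change. These figures rest on a normal true-score model and on population values that the protocol does not give. Other measures are selected only indirectly, so this part applies to them less.

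The consequence is confined to the Aim 1 validation conclusion and the interpretation of within-arm change. Neither the trial's sample size nor its randomised comparison depends on this coefficient. It is a minor improvement rather than a flaw in the trial.

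**What to change.** In Section III, Aim 1, state the type of correlation and keep it for the multi-trait, multi-method matrix. For each measure also report:

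- the mean difference between the two interviews, with a 95% confidence interval;
- a two-way, single-measure, absolute-agreement ICC, with a 95% confidence interval.

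Add a sentence saying that, for the Hopkins and Harvard checklists, enrolment at 1.75 or above restricts the range and produces some regression to the mean, and that the results will be read accordingly.

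The cost is negligible: the same 24 women and the same interviews, with two more summaries per measure. Section III says that the pilot period has not yet started, so the change can be made before any retest data exist.
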